## Discussion

### Significance

Despite the growing popularity of mind–body practices, few studies have investigated their use in the perioperative period during complex surgeries such as cardiac cases. Therefore, using a comparative randomized controlled trial design, this study will lay the foundation to investigate mind–body practices in the perioperative period by exploring the feasibility of IK meditation in patients undergoing heart surgery.

### Future direction

A reasonable compliance to the meditation schedule in the intervention groups will denote feasibility and will lay down the foundation for a more elaborate study. Comparison between the two intervention groups will provide an estimate of the optimal timeframe and duration of the intervention necessary to achieve the desirable outcomes. Sensitive, quantitative tools have been used to examine and measure the magnitude of effect for various outcomes such as pain, sleep, delirium, cognitive decline, depression, anxiety, and inflammatory biomarkers. One or more positive outcomes along with their respective effect sizes will inform on the endpoints and sample size of an adequately powered study in the future.

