### Eligibility criteria

Patients aged ≥ 18 years, undergoing CABG, valve surgery, or isolated aortic surgery will be included in the study. To allow implementation of a prehabilitative strategy, surgeries must be scheduled at least 14 days after enrollment (Table 1).

**Table 1 Tab1:** Study inclusion and exclusion criteria

Inclusion criteria	
1. Aged ≥ 18 years	
2. Undergoing any of the following types of cardiac surgery: CABG with or without valve surgery (aortic and/or mitral); isolated valve surgery; isolated aortic surgery	
3. Surgery scheduled for at least 14 days after enrollment	
Exclusion criteria	
1. Urgent and/or emergent surgery	
2. Non-English speaking	
3. Pre-existing history of psychiatric illness as documented in the medical record or divulged in history taking in pre-enrollment patient interview, such as anxiety, depression, or bipolar disorder	
4. History of cerebrovascular accident or recent history (< 3 months) of seizures	
5. History of dementia, Parkinson’s disease, Alzheimer’s disease, or other forms of cognitive decline	
6. Current use of cognition-enhancing drugs	
7. Current management for chronic pain	
8. Currently enrolled in another interventional study that could impact the primary outcome, as determined by the PI	
9. Educational attainment below high school level or equivalent	
10. Significant visual impairment	
Preoperative dropout criteria	
1. Cognitive impairment as defined by MoCA score < 10	
2. DASS-21 depression score > 10	

Patients undergoing urgent or emergent procedures or those undergoing only minimally invasive cardiac procedures will be excluded. Non-English-speaking patients and those with significant visual impairment will also be excluded, as these factors preclude performing neurocognitive assessments. Patients who do not have high-school level or the equivalent educational attainment, patients with moderate to severe cognitive impairment as defined by baseline Montreal Cognitive Assessment (MoCA) < 10 and those on cognition-enhancing drugs will be excluded. Patients with a history of cognitive impairment and psychiatric illnesses will be excluded. Patients who are actively taking pain medications will be excluded. Patients who are currently enrolled in another interventional study that could potentially impact the primary outcome will also be excluded from the study.

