### Recruitment and randomization

Individuals will be identified from perioperative surgical consult lists and cardiac surgery clinic visit schedules. If a candidate is eligible for enrollment, he or she will be approached by a member of the research team to discuss the study in detail. Written informed consent will be obtained before initiation of any study procedures.

After obtaining consent, enrolled participants will be randomly assigned to one of three groups using block randomization in a 1:1:1 allocation. REDCap will be utilized to implement the randomization schema while maintaining the blind. REDCap is a secure software designed for rapid data capture tools using metadata table referenced by presentation-level operational modules [24]. Patients will be randomized to one of the following groups:Group 1: Patients are asked to meditate twice daily, starting from least two weeks before surgery, up until four weeks after surgery;Group 2: Patients are asked to meditate twice daily from the day after surgery until four weeks after surgery;Group 3: Patients in the control group will undergo surgery and subsequent hospital stay according to the current standard of care, which does not include meditation.

Patients who are actively meditating previously and are willing to participate in the study will be asked to refrain from meditating during the study period if they are randomized to the control group. They will be required to follow the IK meditation schedule during the period of study participation if they are randomized to one of the intervention groups.

The inclusion of a control group will allow for quantification of the natural history of surgery and postoperative complications. Further, we are utilizing two interventional groups to assess whether a prehabilitative strategy results in differences as compared to a mitigation strategy. Two intervention groups will also help us determine the optimal duration of intervention and the possible impact of duration on compliance and other secondary outcomes.

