### Statistical analysis

In this feasibility study, a convenience sample of 30 participants (10 per group) will be enrolled to assess feasibility. While we expect it to be very rare, it is possible that some individuals may be determined ineligible after signing consent (because of their baseline MoCA or DASS-21 depression scores). Therefore, we plan to enroll enough patients to obtain data from 30 randomized participants. We estimate that approximately 40 patients may be enrolled to account for dropouts, loss of follow-up, and to achieve this sample size of 30. No a priori power calculation was performed.

Since the primary outcome of the study assesses the overall feasibility of conducting the trial, our descriptive study will record the proportion of patients eligible who meet inclusion without exclusion criteria and decide to participate. The statistics for overall protocol adherence to the intervention will be recorded by reporting the total number of sessions completed out of that required per protocol. We will also assess the total number of questionnaires completed out of the total required.

Descriptive statistics of data will be performed. Categorical data will be reported as proportions and assessed with the use of a chi-square or Fisher’s exact test. Continuous data will be reported as means ± standard deviations or median (quartile 1 and quartile 3) depending on distribution and assessed using analysis of variance (ANOVA). We estimate that with a small sample size it may not be acceptable to assume normality and may be appropriate to use a non-parametric equivalent such as Kruskal–Wallis test when appropriate. A trajectory analysis will be performed to assess changes in the presence of delirium or changes in cognitive function over time. Since the secondary outcomes are exploratory in nature, all tests will be two-sided, with *p* values < 0.05 considered statistically significant. Data will be analyzed using SAS 9.4 (SAS Institute Inc., Cary, NC, USA) or later. Our primary analysis will be conducted using the intention-to-treat principle. All trial reporting will adhere to the Standard Protocol Items: Recommendations for Interventional Trials (SPIRIT; Additional file 1: Table S1).

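### The Group 1 versus Group 2 comparison is said to give the optimal timeframe and duration, but start time and number of sessions change together across only two regimens, so neither optimum can be estimated.

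*Protocol article*

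**What the plan says.** The two meditation regimens are defined under Recruitment and randomization:

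- "Group 1: Patients are asked to meditate twice daily, starting from least two weeks before surgery, up until four weeks after surgery"
- "Group 2: Patients are asked to meditate twice daily from the day after surgery until four weeks after surgery"

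The third group receives "the current standard of care, which does not include meditation". Eligibility criteria adds that "surgeries must be scheduled at least 14 days after enrollment", which sets a minimum for Group 1's preoperative phase but no maximum.

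The same Recruitment section gives two reasons for having two meditation groups. The first is to see whether a prehabilitative strategy differs from a mitigation strategy. The second begins "Two intervention groups will also help us determine the optimal duration of intervention" and goes on to mention how duration may affect compliance and the other secondary outcomes. Future direction, in the Discussion, is firmer and wider: "Comparison between the two intervention groups will provide an estimate of the optimal timeframe and duration of the intervention".

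Allocation is "using block randomization in a 1:1:1 allocation", and Statistical analysis plans "a convenience sample of 30 participants (10 per group) will be enrolled to assess feasibility". Limitations does not mention that start time and duration vary together.

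**The concern.** The two regimens share an end point and a daily frequency. Starting earlier therefore also means a longer course and more sessions. If Group 1 does better, the result fits a benefit of starting early, a benefit of doing more, or both, and the data cannot say which. Separately, an optimum is a feature of a curve. Two points can show which of two regimens looked better, but not where the best start or the best length lies.

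What is at stake is what the trial may legitimately conclude. The article credits the design with a property that its own arms do not have. A reader who takes the claim at face value would treat a comparison of two packages as evidence on optimal timing and duration.

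**Working it through.** **Planned numbers.** 3 groups × 10 = 30, as stated. The article expects to enrol about 40, which implies a loss of 1 − 30/40 = 25%. As a check, 30 / (1 − 0.25) = 40. The 25% is back-calculated and not stated.

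**Sessions per arm** (assuming 14 preoperative days, 28 postoperative days and two sessions a day):

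- Group 1: 2 × 14 + 2 × 28 = 84 sessions over 42 days
- Group 2: 2 × 28 = 56 sessions over 28 days
- Group 3: 0 sessions
- Difference, Group 1 minus Group 2: 28 sessions, ratio 84/56 = 1.5, all 28 preoperative

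Because 14 days is a minimum, the gap can be wider. With a 21-day preoperative phase, for illustration, Group 1 would have 2 × 21 + 56 = 98 sessions, a ratio of 1.75. That variation follows surgical scheduling and is not randomized, so it cannot be used to separate timing from amount.

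**Can timing and amount be separated?** Let *a* be the effect of doing any meditation, *t* the effect of a preoperative start, and *f(s)* the effect of *s* sessions. The group means give only two contrasts:

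- Group 1 − Group 2 = *t* + [*f*(84) − *f*(56)]
- Group 2 − Group 3 = *a* + *f*(56)

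The first contrast contains *t* and the amount effect only as a sum. The rank of the arm-level design, with amount entered as a linear term, shows the same:

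| Model | Arms used | Parameters | Rank |
|---|---|---|---|
| Intercept, preoperative start, sessions | Groups 1 and 2 | 3 | 2 |
| Intercept, any meditation, preoperative start, sessions | All three | 4 | 3 |
| Intercept, preoperative start, sessions (no separate any-meditation effect) | All three | 3 | 3 |

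Only the last row is identified. It needs *a* = 0 and *f(s)* = *b·s*, which give *b* = (Group 2 − Group 3)/56 and *t* = (Group 1 − Group 2) − 28*b*. The model is then saturated, so its linearity cannot be tested. A straight line also has no interior optimum, so even this route does not deliver what the article promises.

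Purely as illustration, one further arm that changed the number of sessions while keeping the start fixed would raise the second row to rank 4 of 4. Timing and amount would then be separable under the linear term. Locating an optimum would still need several levels of each.

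**Precision, as context only.** With 10 analysed per arm, the standard error of the standardised difference is √(2/10) = 0.447, and the 95% half-width is 2.101 × 0.447 = 0.94 SD. If all 40 in the abstract were randomized, about 13 per arm, it is 2.064 × √(2/13) = 0.81 SD. The identification problem is the same at either size.

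**The case against.** The strongest defence is that nothing in the plan depends on the claim. The primary outcome is feasibility through diary adherence. Statistical analysis contains no regimen-selection rule and no duration model. The firmer of the two sentences is in the Discussion. This stands, and it limits the reach of the point to what may be concluded.

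Second, the article calls all secondary outcomes hypothesis generating, describes a convenience sample and says that no power calculation was done. Imprecision is therefore largely disclosed and is not a separate fault. Those statements concern strength of evidence, however. They do not separate two factors that the arms never vary separately, and no sample size would.

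Third, timeframe and duration could be read jointly, as asking which of the two tested packages looks better. That reading is possible for Future direction. It is weakened by the Recruitment sentence, which names duration alone, and it still leaves the word optimal unsupported.

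Fourth, the Recruitment section already states a contrast that the design can support, prehabilitation versus mitigation, and its second reason includes a legitimate comparison of compliance. Both should be kept.

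A reader might also infer that the next trial's regimen will be chosen on this contrast. The article does not say so. Future direction says that positive outcomes and their effect sizes will inform the endpoints and sample size of a later study, and Ethics and dissemination makes larger studies conditional on feasibility.

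**Conclusion.** The point holds as an overstatement of what the two-group comparison can show. Start time and amount are fully confounded (84 against 56 sessions for a 14-day start), two regimens cannot locate an optimum, and the control arm does not resolve this without an untestable linear dose assumption. Nothing elsewhere in the article withdraws the claim.

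The session counts rest on 14 preoperative and 28 postoperative days at two sessions a day. The confounding itself rests only on the shared end point and frequency, so it does not depend on those counts. The ±0.94 SD assumes 10 analysed per arm and is supporting context. The documents do not support extending the point to the feasibility conclusion or to how a later trial's regimen would be selected.

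**What to change.** **Future direction.** Replace the sentence with wording such as: *The Group 1 minus Group 2 contrast will give an exploratory estimate, with 95% confidence interval, of the combined effect of adding the preoperative phase to the postoperative programme (earlier start and more sessions together). The trial will not identify an optimal timeframe or duration.*

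**Recruitment and randomization.** Leave the prehabilitation-versus-mitigation reason as it is. In the next sentence remove only the clause about determining the optimal duration, and keep the comparison of compliance and secondary outcomes, worded for example: *Two intervention groups also allow compliance and other secondary outcomes to be compared between the longer programme with a preoperative phase and the shorter, postoperative-only programme.* The compliance comparison needs this description because it has the same confounding: a longer course and a preoperative setting come together.

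The cost is wording in two places and a more modest claim. No arm, schedule, sample size, outcome or test changes; the only reporting addition is the confidence interval.

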**Methods:**

This is a prospective, randomized controlled feasibility trial. A total of 40 adult patients undergoing cardiac surgery will be randomized to one of three study groups. Participants randomized to either of the two intervention groups will receive meditative intervention: (1) commencing two weeks before surgery; or (2) commencing only from the day after surgery. Meditative intervention will last for four weeks after the surgery in these groups. Participants in the third control group will receive the current standard of care with no meditative intervention. All participants will undergo assessments using neurocognitive, sleep, depression, anxiety, and pain questionnaires at various time points in the perioperative period. Blood samples will be collected at baseline, preoperatively, and postoperatively to assess for inflammatory biomarkers. The primary aim of this trial is to assess the feasibility of implementing a perioperative meditative intervention program. Other objectives include studying the effect of meditation on postoperative pain, sleep, psychological wellbeing, cognitive function, and delirium. These will be used to calculate effect size to design future studies.

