### Aims and objectives

We hypothesized that it is feasible to implement a meditation program aimed at improving outcomes in the adult cardiac surgical population. The primary aim of this pilot study is to assess the feasibility of implementing a meditation program in the preoperative period, which will be measured in terms of adherence of the participants to the meditative regimen. Our study will further explore whether a perioperative meditation regimen can result in improvement in postoperative outcomes including pain, sleep, psychological wellbeing, cognitive function, and delirium. Given the pilot nature of the proposed trial, all secondary outcomes will be considered hypothesis generating only.

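### Planning the next trial on favourable secondary effects from about 10 patients per arm is expected to inflate the effect size and underpower that trial

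*Protocol article*

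**What the plan says.** Three parts of the protocol article bear on this point.

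- **Use of the secondary results.** Discussion, Future direction: "One or more positive outcomes along with their respective effect sizes will inform on the endpoints and sample size of an adequately powered study". The Abstract (Methods) says of the secondary objectives: "These will be used to calculate effect size to design future studies".
- **Size and testing.** Statistical analysis: "a convenience sample of 30 participants (10 per group) will be enrolled to assess feasibility", with about 40 enrolled to reach that number, and "No a priori power calculation was performed". For the secondary outcomes, "all tests will be two-sided, with *p* values < 0.05 considered statistically significant". Continuous outcomes are compared by three-group ANOVA or Kruskal–Wallis, categorical ones by chi-square or Fisher's exact test.
- **Status of the results.** Aims and objectives: "all secondary outcomes will be considered hypothesis generating only". Study outcomes repeats this.

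Future direction lists seven outcome domains: pain, sleep, delirium, cognitive decline, depression, anxiety and inflammatory biomarkers. Several have more than one instrument or time point. The article does not say what makes an outcome positive.

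**The concern.** Supplying planning values for a later trial is the stated purpose of the secondary data. An estimate that is used only because it came out favourably is biased upward, and the bias is large when the sample is small. With 10 per arm, sampling error in a standardized difference is about as large as a moderate effect, so the outcomes that stand out will tend to be those where chance helped most. A trial planned on such a value may pursue the wrong endpoint and enrol too few patients to detect the effect that really exists.

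The hypothesis-generating label does not prevent this. It limits what may be claimed about efficacy. It does not limit use of the estimates for choosing an endpoint and a sample size, which is what Future direction and the Abstract intend.

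**Working it through.** **Inputs from the article.** 10 per arm (30 in all), two-sided 0.05, three groups, seven named domains. There is no powered sample size to reproduce. The only arithmetic is 3 × 10 = 30, and 40 enrolled to keep 30 implies a loss of 1 − 30/40 = 25%.

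**Assumptions.** The article gives no true effect and no SD. The true standardized difference d is therefore varied. Outcomes are treated as continuous and normal, comparisons as pairwise, and estimates as used without discount. Simulations used 200,000 trials per scenario.

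**Step 1. Smallest pairwise difference that reaches p < 0.05.** Observed d = t(0.975, df) × √(2/10).
- Two-sample t-test, 18 df: 2.101 × 0.447 = 0.94.
- Error df of the three-group ANOVA, 27: 2.052 × 0.447 = 0.92.
- The omnibus F test needs F(0.95; 2, 27) = 3.354, so eta-squared = 2 × 3.354 / (2 × 3.354 + 27) = 0.20.

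**Step 2. If positive means p < 0.05 (18-df t-test).** The table gives the mean favourable significant estimate. It then gives the per-arm size that estimate implies at 80% power, n = 2 × [(1.960 + 0.842)/d]², rounded up; the power such a trial really has, Φ(d/√(2/n) − 1.96); and the size the assumed true d requires.

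| Assumed true d | Mean significant estimate | Ratio to truth | n per arm planned | Actual power | n per arm needed |
|---|---|---|---|---|---|
| 0.2 | 1.18 | 5.9 | 12 | 7% | 393 |
| 0.3 | 1.20 | 4.0 | 11 | 10% | 175 |
| 0.5 | 1.24 | 2.5 | 11 | 22% | 63 |
| 0.8 | 1.32 | 1.65 | 10 | 43% | 25 |

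For true d up to 0.8 every significant favourable estimate exceeds the truth, because the threshold itself does. For larger effects the bias fades: the mean significant estimate is 1.39 at true d = 1.0 and 1.67 at 1.5. A follow-on trial sized on the selected estimate falls short of 80% power in 88% of cases at d = 1.0, 64% at 1.3 and 48% at 1.5.

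**Step 3. If positive means the most favourable of seven independent outcomes, with no p-value rule.** The mean selected d is about 0.64 when no outcome has any effect, and 1.08 when every true d is 0.4. Planning on 1.08 gives 2 × (2.802/1.08)² = 13.5, so 14 per arm (15 with a t correction). Actual power at d = 0.4 is then about 18%, and about 100 per arm would be needed.

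**Step 4. Chance findings.** With seven independent outcomes and no true effect, P(at least one p < 0.05) = 1 − 0.95⁷ = 0.30. Correlation lowers this; several tools and time points per domain would raise it.

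**Step 5. No selection.** If an outcome's estimate is used whatever it shows, its mean is close to the truth (0.52 for a true 0.5). It is very imprecise: for an observed d of 0.5 the 95% interval is 0.5 ± 1.96 × √(2/10 + 0.5²/40), or −0.39 to 1.39.

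**The case against.** The strongest reply is that the article fixes no such rule. Future direction says that results will inform the next study, not that they will determine it. Positive is undefined, and the 0.05 threshold stands in Statistical analysis without any link to planning. The Abstract mentions effect sizes without any selection. Ethics and dissemination names sleep, postoperative pain and cognitive decline as the subjects of larger studies, conditional on feasibility and not on favourable results. Future direction also makes reasonable compliance the foundation for going further.

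Much of this stands. A reader might infer that the next endpoint and sample size will be taken straight from outcomes with p < 0.05, so that an underpowered trial is guaranteed. The text does not support that. It would require positive to mean significant, the estimate to be used undiscounted, and a true d below about 0.94. Nor are nominal, unadjusted tests an error in themselves when outcomes are labelled exploratory, and multiplicity detail may lie in an analysis plan that is not shown.

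The reply does not remove the selection. Future direction ties both endpoint and sample size to positive outcomes and their own effect sizes, and Step 3 shows inflation without any p-value threshold. The unselected reading of the Abstract avoids the bias but leaves an interval too wide to plan on.

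**Conclusion.** The concern holds as an expected bias, not a certainty. Under either plausible reading of positive, the selected effect from 10 per arm is expected to be well above the truth for small to conventionally large effects. It is about 1.2 to 1.3 for a true d of 0.2 to 0.8 if selected on significance. If selected as the best of seven, it is about 0.64 under no effect and 1.08 for a true d of 0.4. A trial sized on the mean significant estimate would have roughly 7% to 43% power over the range 0.2 to 0.8.

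These figures rest on assumed true effects, normal continuous outcomes, pairwise contrasts and, for the seven-outcome results, independence. They do not apply directly to a binary outcome such as delirium. The consequence falls on the next trial and on what this pilot can say about its own stated purpose. The primary feasibility outcome, randomization and conduct are untouched.

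**What to change.** Reword the sentences in Future direction and in the Abstract so that:

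- the next endpoint is chosen on clinical relevance, completion rate and measurement properties (Ethics and dissemination already names candidates, and Statistical analysis already records questionnaire completion);
- SDs, event rates and attrition are taken from this trial with their confidence limits;
- the next trial is sized on a minimum important difference, not on the effect observed here;
- all secondary contrasts are reported with 95% confidence intervals, whether favourable or not, and any p-values are described as nominal.

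Dropping the significance label altogether is a matter of preference and is not needed.

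The cost is wording only, with no change to design, visits or data collection. The downside is that the paper can no longer offer an observed effect size as the planning value for its successor.
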